#### Step 10: run with joy

### Sample size

Based on our previously conducted RCT, an injury incidence of 38% is expected in recreational runners participating in running events (10 km up to 42.195 km).^11^ The sample size calculation is based on the subgroup analysis on runners with previous injuries. With a risk difference of 5%, a significance level of 0.05 (two-sided testing and a power of 80%), a minimum of 1414 runners with a previous injury in the previous 12 months should be included in the analyses. The sample size is doubled in order to obtain enough power for the primary analyses in the entire study population. Taking a loss to follow-up of 20% into account, a total of 3394 runners (1697 in each group) should be included.

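### The 1414 previously injured runners said to give 80% power are about one arm's requirement; as a two-arm total they give about 50%

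*Protocol article*

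**What the plan says.** The Sample size section of the protocol article takes its event rate from the investigators' previous trial: "an injury incidence of 38% is expected in recreational runners participating in running events". It names the analysis that sets the size: "The sample size calculation is based on the subgroup analysis on runners with previous injuries". The remaining inputs are a 5% risk difference, a two-sided significance level of 0.05 and 80% power. The result is that "a minimum of 1414 runners with a previous injury in the previous 12 months should be included in the analyses".

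The next step reads: "The sample size is doubled in order to obtain enough power for the primary analyses in the entire study population". After an allowance of 20% for loss to follow-up, the target is 3394 runners, 1697 in each group.

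As worded, 1414 is the number of previously injured runners in the analyses over both arms, and the doubling takes that subgroup to the whole study population.

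**The concern.** A 5-point difference from a base rate near 38% usually needs well over 1000 runners per arm. A two-arm total of 1414 is therefore too small on its face, by a factor of about two. The doubling that follows looks like the step that adds the second arm, but the text gives it another purpose, namely powering the entire population.

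The subgroup is not a side issue here. The sample size is expressly based on it, the Discussion says the programme is aimed at runners with earlier injuries, and the injury proportion in previously injured runners is a named secondary outcome. A reader who trusts the paragraph would take a non-significant subgroup result as coming from a comparison with an 80% chance of detecting the planned effect.

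**Working it through.** **Inputs** (Sample size section, except the last)

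- Expected injury proportion: 38%, taken as the control rate, so 38% versus 33%.
- Two-sided alpha 0.05 (z = 1.960); power 80% (z = 0.842).
- Stated subgroup number: 1414. Final target: 3394, or 1697 per group.
- Equal allocation (Study design section).

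**Step 1: the plan's own enrolment figure**

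- 1414 × 2 = 2828; 2828 × 1.2 = 3393.6, which rounds to 3394.
- 1414 × 1.2 = 1696.8, which rounds to 1697, the stated number in each group.

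The final target is thus exactly what an ordinary two-arm calculation with 1414 per arm would give.

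**Step 2: runners needed for 38% versus 33%**

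Unpooled variance:

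n per arm = (1.960 + 0.842)² × (0.38 × 0.62 + 0.33 × 0.67) / 0.05²
= 7.849 × (0.2356 + 0.2211) / 0.0025
= 1434

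Pooled variance, with mean rate 0.355:

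n per arm = [1.960 × √(2 × 0.355 × 0.645) + 0.842 × √(0.2356 + 0.2211)]² / 0.05² = 1437

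The total over two arms is 2868 to 2874. With continuity correction it is 1477 per arm, 2954 in total.

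**Step 3: can any variant give 1414 as a total?**

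| Variant | Total needed |
|---|---|
| 38% vs 33%, two-sided | 2868 to 2954 |
| 40.5% vs 35.5%, two-sided | 2951 to 3036 |
| 38% vs 43%, two-sided | 3018 to 3104 |
| Same rates, one-sided | 2264 to 2462 |

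None does. With a 5-point difference, the control rate would have to be about 15.5% (15.5% versus 10.5% needs 709 per arm). As a per-arm number, 1414 fits well: it is within 1.6% of 1437, and a control rate of 36.8% gives it exactly. The previous trial's control rate of 36.7%, quoted in the Introduction, gives 1412.

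**Step 4: power with 1414 in total (707 per arm)**

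- Standard error under the null: √(2 × 0.355 × 0.645 / 707) = 0.02545.
- Standard error under the alternative: √(0.4567 / 707) = 0.02542.
- Power = Φ[(0.05 − 1.960 × 0.02545) / 0.02542] = Φ(0.005) = 50.2%.
- With 38% as the lower rate (38% versus 43%), power is 48.2%.
- If the subgroup's rate is higher (assumed values): 45% versus 40% gives 47.7%, and 50% versus 45% gives 46.9%.
- The difference detectable with 80% power at 707 per arm is about 7.1 points (38% versus 30.9%).

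**Step 5: subgroup power by the share of runners with a previous injury**

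The article does not give this share, so the values below are assumptions, applied to 2828 analysed runners.

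| Assumed share | Subgroup total | Power, 38% vs 33% |
|---|---|---|
| 40% | 1131 | 42% |
| 50% | 1414 | 50% |
| 60% | 1697 | 58% |
| 70% | 1980 | 64% |
| 100% | 2828 | 79% |

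**Step 6: the primary analysis in all runners**

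2828 analysed (1414 per arm) gives 79.4% power for 38% versus 33%. If 20% of 3394 are lost, about 2715 remain and power is 77.7%.

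**The case against.** The arithmetic is hard to contest, but its reach can be.

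- **The primary analysis is adequately sized.** This is correct: power is close to 80% for all participants. The error concerns the subgroup claim and does not mean that the trial as a whole is too small.
- **The origin of the error is an inference.** The enrolment figure may have been calculated correctly for the whole population, with the sentences on the subgroup and the doubling describing it wrongly. The article cannot settle this, and the point stands. It does not rescue the claim, because the subgroup would then need about 2828 previously injured runners, all of those to be analysed. The Participants section sets no such entry criterion, and Step 1 of the programme is written for runners without earlier injuries.
- **1414 is a minimum, so the subgroup may be larger.** This is also fair, and 50% should be read with the range in the Step 5 table. No share below 100% brings power to 80%, and even 100% gives only 79%.
- **Confidence intervals are already planned.** The Statistical analysis section provides for differences and odds ratios with 95% intervals, so imprecision would be visible. That limits the harm but does not make the stated power true.

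**Conclusion.** The concern holds. The stated inputs require about 2870 previously injured runners over both arms, and the 1414 stated is half of that. At 1414, power for the 5-point difference is about 50%, and 80% power is reached only for about 7 points. The result rests on 38% versus 33%, two-sided 0.05 and equal arms. Moving the 38% to the lower rate or midway, or raising the assumed subgroup rate to 50%, keeps power between 47% and 50%. If 40% to 60% of the runners analysed had a previous injury, power would be 42% to 58%.

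The primary comparison in all runners keeps about 78% to 79% power. The correction matters because the article bases its sample size on this subgroup and the programme is aimed at it.

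**What to change.** Rewrite the Sample size paragraph in four respects.

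1. State that 80% power for 38% versus 33% needs about 1434 to 1437 previously injured runners per arm, about 2870 in total.
2. State that 1414 such runners in total (707 per arm) give about 50% power for 5 points, or 80% power for about 7 points. Give the expected share of previously injured runners, or a range, with the power that follows.
3. Replace the sentence on doubling: 2828 analysed runners are two arms of 1414 and give about 79% power for the primary comparison in all participants. Drop the statement that the calculation is based on the subgroup.
4. Commit to interpreting the subgroup by its confidence interval, set against the 5-point and 7-point figures.

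The cost is a reworded paragraph and a less favourable statement of subgroup power. Enrolment, randomisation and data collection do not change.

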Although the injury prevention programme of the INSPIRE trial was not effective, some interesting and new insights were gained.^11^ For example, it appeared that the multifactorial online prevention programme seemed to have a negative effect on the occurrence of RRIs in runners with no injury history.^11^ Furthermore, the results showed that runners who applied the information from the biomechanics section of the prevention programme to their training seemed to have an increased injury risk compared with those who did not use this information.^11^ We assume this is the result of the advice on stride pattern. These findings indicate that research on RRI prevention should probably specifically aim at runners who had RRIs in the past. Moreover, advices on stride pattern should not be presented through a website, since this seems to have negative impact on injury occurrence. Probably changes to stride pattern should only be made under supervision of a trainer or physiotherapist.^12^ Participants of the INSPIRE trial indicated that ‘not knowing what to do’ was an important barrier for injury prevention and the participants wished to integrate the injury prevention measures into their training sessions.^13^ This indicates that injury prevention advices should be directive and personalised.

Therefore, we designed an enhanced, online multidisciplinary injury prevention programme entitled ‘10 steps 2 outrun injuries’. The primary aim of this study is to test the effectiveness of this injury prevention programme on the number of RRIs in recreational runners.

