#### Step 1: do not change anything if you have no experience with running injuries

A previous injury is the most important risk factor for a new RRI.^4 14^ Furthermore, the results of the INSPIRE trial showed that the prevention programme seemed to have a negative impact in runners who did not suffer an RRI before.^11^ Therefore, runners without previous RRIs are advised not to change anything in their running behaviour. This is a general advice, that is not further specified to specific parts of running behaviour. Furthermore, all steps of the prevention programme are visible to runners without a history of RRIs. This is to enable them to start using the programme if they do experience pain during running in the future.

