## Discussion

Injuries are a major problem among runners, for which no effective prevention measures have been identified so far. Therefore, the aim of this RCT is to examine the effectiveness of an online injury prevention programme. This programme is aimed at runners who previously suffered from RRIs and includes 10 steps that all deal with one component of running injury prevention. The programme is tested in a large group of runners. Therefore, subgroup analyses based on previous injuries, sex, running experience, distance of running event registered for and injury locations will be possible. Because the programme is presented on a website and mobile application, the programme has the ability to be easily implemented and applied to large and diverse groups of runners if it proves to be effective.

A potential limitation of this study is the use of self-reported RRIs. Runners who are performing with pain may give diverse responses regarding the presence of an RRI. This is partly solved by including the OSTRC Overuse Injury Questionnaire in the follow-up questionnaires, which gives more insight in the severity of the reported RRIs. However, also this questionnaire is patient-reported and subject to the interpretation of the runners. Another possible limitation is that some of the advices in the prevention programme may be subject to the interpretation or motivation of the runners. A runner may, for example, adjust the score on the Numerical

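### Doubling the sample gives about 80% power for the whole-population primary analysis only if runners advised to change nothing benefit as much as the previously injured, and the 1414 behind it is a per-arm number

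*Protocol article*

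**What the plan says.** The Sample size section of the protocol article starts from the target subgroup: "The sample size calculation is based on the subgroup analysis on runners with previous injuries". It takes an injury incidence of 38% (given for event runners in general), a risk difference of 5%, two-sided 0.05 and 80% power. It concludes that at least 1414 runners injured in the previous 12 months must be analysed. The step to the whole trial is one sentence: "The sample size is doubled in order to obtain enough power for the primary analyses in the entire study population". A 20% allowance for loss then gives 3394, or 1697 per group. The section states no separate effect for the whole population and no expected share of previously injured runners.

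Under Outcome measures, the comparison of all runners is primary and the comparison in previously injured runners is secondary.

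Three other places bear on the size of the effect:

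- Step 1: "runners without previous RRIs are advised not to change anything in their running behaviour". It adds that all steps remain visible to these runners.
- Discussion: "This programme is aimed at runners who previously suffered from RRIs".
- Introduction, drawing on the earlier trial: "research on RRI prevention should probably specifically aim at runners who had RRIs in the past".

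**The concern.** The 5-point difference is set for the group the programme is meant to help. The primary test also includes runners who are advised not to alter their running. If they gain less, the overall difference is a weighted average below 5 points. A larger sample makes up for that only if it was sized for the smaller difference, and nothing in the section does this.

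At stake is how a null primary result would be read. A programme that works as assumed in its target group could miss significance overall more often than the stated 80% power suggests, and then be reported as ineffective. The subgroup result that would correct that reading has its own problem: the number quoted for it does not give the stated power.

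**Working it through.** **Inputs.** From Sample size: control risk 38%, difference 5 points (read as 38% vs 33%), two-sided 0.05, 80% power, 1414, doubling, 20% loss, 3394. Assumptions not in the document: the share *s* of previously injured runners, the effect *e* in the other runners, and the same 38% control risk in both groups.

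**1. The plan's own figure.** Pooled formula for two proportions, per arm:

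n = [1.960·√(2·p̄·(1−p̄)) + 0.842·√(p₁(1−p₁) + p₂(1−p₂))]² / d²

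With p₁ = 0.38, p₂ = 0.33, p̄ = 0.355 and d = 0.05:

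n = [1.960·√0.45795 + 0.842·√0.4567]² / 0.0025 = (1.326 + 0.569)² / 0.0025 ≈ 1437 per arm, or 2874 in total.

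The unpooled formula gives 1434 per arm. Starting from 37% vs 32% gives 1415 to 1418 per arm. A one-sided test gives 1132 per arm (2264 in total). So 1414 is matched, within about 2% of 1437, only as a per-arm number. No variant tried gives it as a total.

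**2. The chain to 3394.** 2 × 1414 = 2828, and 2828 × 1.2 = 3393.6, so 3394. After 20% loss, 3394 × 0.8 ≈ 2715 remain.

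**3. Power of the subgroup as worded.** Power = Φ{[d·√n − 1.960·√(2·p̄·(1−p̄))] / √(p₁(1−p₁) + p₂(1−p₂))}, with n per arm.

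For 1414 in total (707 per arm): (0.05·√707 − 1.326)/0.676 = (1.329 − 1.326)/0.676 ≈ 0.005, so power is about 50%. The difference detectable with 80% power is about 7.1 points.

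**4. Power of the primary analysis if 5 points holds in everyone.** With 1414 per arm: (1.880 − 1.326)/0.676 ≈ 0.82, so 79%. With 2715 analysed it is 78%.

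**5. Power if the effect is smaller in the other runners.** The overall difference is s·5 + (1−s)·e points. For s = 50% and e = 0 it is 2.5 points (38% vs 35.5%): (0.025·√1414 − 1.336)/0.682 = (0.940 − 1.336)/0.682 ≈ −0.58, so 28%. The same formula with 2828 analysed gives:

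| Share previously injured (assumed) | Overall difference, e = 0 | Power | Overall difference, e = 2.5 | Power |
|---|---|---|---|---|
| 40% | 2.0 | 20% | 3.5 | 49% |
| 50% | 2.5 | 28% | 3.75 | 55% |
| 60% | 3.0 | 38% | 4.0 | 60% |
| 70% | 3.5 | 49% | 4.25 | 65% |
| 90% | 4.5 | 70% | 4.75 | 75% |
| 100% | 5.0 | 79% | 5.0 | 79% |

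With 2715 analysed, the 50% row becomes 27% and 53%.

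**6. What the doubling does.** Because 1414 is a per-arm size, multiplying by two only adds the second arm. It contains no allowance for dilution. Even a correctly sized subgroup total of 2874, doubled to 5748, would have only 50% power for 2.5 points.

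**The case against.** The best defence is that the power claim is true on one reading: if 5 points is the difference expected in all runners, 2828 gives 79%, which is 80% for practical purposes. That stands. The sample cannot be said flatly to leave the primary analysis underpowered.

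A reader might go further than the document allows in four ways.

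- *The effect in the other runners is zero by design.* Step 1 is described as general advice, all steps stay visible so that these runners can start using them if they get pain, and newsletters to the whole intervention group highlight the content. Step 1 also concerns runners with no injury experience, whereas the sample-size subgroup is defined by the previous 12 months. Runners with only older injuries fall outside that subgroup but are not told to change nothing. Zero is one end of a range.
- *The doubling implies that half the runners are previously injured.* The text gives power as the reason for doubling, and since 1414 is a per-arm size, the factor of two says nothing about the share. The 28% is one scenario.
- *The primary test has less power than the subgroup test.* At a 50% share this holds with zero effect elsewhere (28% against 50%) but reverses with half the effect (55% against 50%).
- *The subgroup should therefore be tested first, as a gate to the whole-population test.* That changes the trial's primary question and places it behind a test with about 50% power at a 50% share. The numbers do not require it.

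It is also fair to say that the target-group result is not lost. It is a named secondary outcome, with a planned subgroup analysis.

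**Conclusion.** The statement that doubling secures enough power for the whole population depends on an unstated assumption that sits badly with the protocol's own rationale: a full 5-point effect in runners advised to change nothing. Without it, power is below the stated 80% at every share examined. It ranges from 20% to 70% with no effect in the other runners (shares of 40% to 90%), and is about 55% to 65% with half the effect in them (shares of 50% to 70%). These figures rest on assumed shares and effects and on a common 38% control risk. That some loss of power follows from a smaller effect does not depend on which share is chosen.

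The second part needs no assumption about dilution: 1414 previously injured runners in total, as worded, give about 50% power for 5 points, not 80%.

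**What to change.** In the Sample size section:

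- state the effect assumed for the whole population and the expected share of previously injured runners;
- give whole-population power as a range over plausible shares and effects in the other runners, with 79% shown as the case of a uniform 5-point effect;
- correct 1414 to a per-arm number;
- restate the power of the previously injured comparison (about 50% with 1414 in total).

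Keep the whole-population comparison primary. In Statistical analysis, add a treatment-by-previous-injury interaction to the planned subgroup analysis, so that a null overall result is not read as no effect in the target group.

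The cost is that the stated power becomes less favourable. No extra participants or data are needed.

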**Methods and analysis:**

For this randomised controlled trial, we aim to include 3394 recreational runners aged 18 years or older who register for a running event (distances 10 to 42.2 km). During the preparation for the running event, runners in the intervention group get access to the enhanced online injury prevention programme. This online programme consists of 10 steps, all covering separate items of RRI prevention. Runners in the control group will follow their regular preparation. With three follow-up questionnaires (1 month before, 1 week before and 1 month after the running event), the proportions of self-reported RRIs in the intervention group and the control group are compared.

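### The 20% loss to follow-up is applied as ×1.2 instead of ÷0.8, so 3394 runners allow for a 16.7% loss and leave about 2715, not 2828, to analyse at 20%

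*Protocol article*

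**What the plan says.** The Sample size section of the protocol article builds the target in four steps.

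- Event rate: "an injury incidence of 38% is expected in recreational runners participating in running events". The planned risk difference is 5%, tested two-sided at 0.05 with 80% power.
- Number to analyse: "a minimum of 1414 runners with a previous injury in the previous 12 months should be included in the analyses".
- Doubling: "The sample size is doubled in order to obtain enough power for the primary analyses in the entire study population". The result, 2828, is not printed.
- Attrition: "Taking a loss to follow-up of 20% into account, a total of 3394 runners (1697 in each group) should be included".

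The abstract, under Methods and analysis, repeats the total: "we aim to include 3394 recreational runners aged 18 years or older". The article gives no other loss rate and no other rule for inflating the sample.

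**The concern.** The section names a number needed for analysis, a loss rate and a number to enrol. These three must agree: the enrolled number less 20% should return the number needed. It does not, because the allowance was added as 20% of the number to be analysed, whereas the loss will be taken from the larger number enrolled.

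What is at stake is modest. If attrition runs exactly as planned, the trial ends below its own implied analysis target and somewhat below its stated power. Anyone who later compares actual attrition with the plan would believe the design tolerates 20% when it tolerates about one in six.

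**Working it through.** **Inputs, all from the Sample size section:** 1414 runners as the minimum to analyse; doubling; 20% loss; 3394 in total and 1697 per group; event rate 38%; difference 5%; two-sided 0.05; power 80%.

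**1. Reproducing the printed totals.**
- 2 × 1414 = 2828.
- 2828 × 1.2 = 3393.6, rounded up to 3394.
- 1414 × 1.2 = 1696.8, rounded up to 1697.

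Both figures match exactly, so the rule used was n × (1 + loss).

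**2. The rule that fits a loss rate.** If N are enrolled and a share d is lost, N × (1 − d) remain, so N = n / (1 − d).
- 2828 / 0.8 = 3535 (3536 for equal groups), which is 141 more than 3394.
- Check: 3535 × 0.8 = 2828.

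**3. What 3394 delivers.**
- After a 20% loss: 3394 × 0.8 = 2715.2, about 2715.
- Shortfall: 2828 − 2715 = 113, and 113 / 2828 = 4.0%.
- Largest loss that still leaves 2828: 1 − 2828/3394 = 16.7%.

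**4. Effect on whole-population power.** The article does not print the second proportion. I read the 5% as an absolute reduction, 38% to 33%, with mean proportion 0.355. With n per arm, the normal approximation gives

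power = Φ{ [0.05 − 1.96 × √(2 × 0.355 × 0.645 / n)] / √[(0.38 × 0.62 + 0.33 × 0.67) / n] }.

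- 2828 analysed (n = 1414): (0.05 − 1.96 × 0.01800) / 0.01797 = 0.82, power 79.4%.
- 2715 analysed (n = 1357.5): (0.05 − 1.96 × 0.01837) / 0.01834 = 0.76, power 77.7%.

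The cost is about 1.6 points before rounding.

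**5. Effect on the previously injured runners.** The article gives no share of runners with an injury in the previous 12 months, so this step is conditional on an assumed share.

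| Assumed share | Previously injured among 2828 | Among 2715.2 |
|---|---|---|
| 40% | 1131 | 1086 |
| 50% | 1414 | 1358 |
| 60% | 1697 | 1629 |

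At any share the count is 4.0% lower. The minimum of 1414 is still met after a 20% loss if the share is at least 1414 / 2715.2 = 52.1%. At a share of 50%, and if 1414 is the two-arm total, the same formula gives 50.2% power at 707 per arm and 48.6% at about 679 per arm, again a cost of about 1.6 points.

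**The case against.** Four points can be made on the other side.

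- *The figure 2828 is never printed or called a minimum.* True: the only stated minimum is 1414 previously injured runners. But 2828 is what doubling 1414 gives, and both printed totals reproduce exactly from that chain. It is fair to call it implied, not stated.
- *The 20% may have been meant as a mark-up on the analysed number.* The wording describes a loss to follow-up, which is a share of those who entered. If a mark-up was meant, the corresponding loss is 16.7%, and the text should say so.
- *The effect is small and the 20% is itself a guess.* This stands, and it is why the point is minor. The article plans confidence intervals, so the achieved precision will be visible, and no analysis changes. There is no slack to absorb the error, however: on the 38% versus 33% reading, 2828 analysed already gives slightly less than 80%.
- *Recruiting more is not a text edit.* This also stands. Enrolment is tied to named running events, and data collection is due to end in May 2020.

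Two stronger readings are tempting. A reader might infer that this error cuts power among previously injured runners to 48.6%. The documents do not support that. If 1414 is the two-arm total, power there is already 50.2% before any attrition error, because 1414 is close to the per-arm number for 38% versus 33% (1437 by the same approximation). That is a separate issue with the base figure. A reader might also infer that the minimum of 1414 will necessarily be missed. That depends on a share of previously injured runners which the article does not give.

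**Conclusion.** The arithmetic is wrong as printed, and nothing elsewhere in the article repairs it. A total of 3394 is consistent with 2828 analysed only up to a 16.7% loss. At the stated 20% it yields about 2715. The shortfall is 113 runners and about 1.6 points of whole-population power.

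The counts rest only on printed figures and the doubling. The power figures also rest on reading the 5% as 38% versus 33%, equal groups and a normal approximation. Any statement about the previously injured subgroup rests further on an assumed share. The error concerns the inflation step alone and holds whatever is concluded about the 1414. Severity is minor.

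**What to change.** Amend the attrition sentence in the Sample size section in one of two ways:

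- keep 3394 and say that it allows for a loss of 16.7%; or
- keep the 20% loss and say that about 2715 runners are then expected in the analysis, with power of about 78% for 38% versus 33%.

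Either costs one sentence and leaves the total in the abstract unchanged. The second makes the stated power slightly less favourable.

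If the sponsor regards 2828 analysed at 20% loss as binding, the matching total is 3535 (3536 for equal groups), and the abstract would have to change with it. That means enrolling about 141 more runners, and the correction does not require it. By the approximation above it would restore 79.4%, not a full 80%.
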